### Safety outcomes

2.9

The safety outcomes include vital signs and laboratory examinations, all of which will be performed in weeks 0 and 4. Vital signs include body temperature, respiration rate, heart rate, and blood pressure. Laboratory tests—ECG and blood routine, urine routine, and stool routine tests—will be used to evaluate occult blood, liver function (alanine aminotransferase, aspartate aminotransferase, γ-glutamyl transpeptidase, total bilirubin, and alkaline phosphatase levels), and renal function (urea nitrogen and Crea levels). The severity and incidence of AEs or reactions will be recorded in detail.

### Patient and public involvement

2.10

As a preliminary study, we surveyed 7 outpatients with angina pectoris and created the “angina treatment diary” on WeChat. This questionnaire has 6 items:

(1)participant number/name;(2)angina number today;(3)angina severity;(4)angina duration;(5)nitroglycerin/SuxiaoJiuxin Pill dosage;(6)a photo of the DLT.

Because the drop-down option is set, a patient can complete it within 1 minute, so this questionnaire will not bore patients. In addition, we will investigate the TCM efficacy. Because participants may not grasp how to judge the changes of their “syndromes,” which will hinder the dissemination of research conclusions to some extent, we converted the abstract concept of “syndrome” into an assessment scale containing clinical symptoms and signs, which we present in a simple and clear way. This scale was created based on early clinical practice, cross-sectional surveys, and literature searches. It has also been examined and improved by patient representatives. The results of this TCM scale can make the effects of DLT understood by patients who want to try TCM therapy, which would promote the use of DLT. In brief, patient and public involvement are necessary for the design, conduct, report, and dissemination of this research. After the statistical analysis, the results will be disseminated to the public via academic conferences and peer-reviewed journals. The patients will be informed of the final results through WeChat.

### Sample size estimation

2.11

As the trial is a superiority trial, we use the non-zero null test in Power Analysis and Sample Size (version 11) for sample size estimation. In a previous study,^[31]^ the mean (and standard deviation) of the angina frequency in the treatment group was 1.90 ± 0.45 per week, and that in the reference group was 2.55 ± 1.03 per week. We wanted to make the most conservative estimate, so we considered the superiority margin as 0 and the true difference as 0.65. Based on a 2-sided test size of a level of 5% (*α* = 0.05), a power of 90% (*β* = 0.1), and equal sample sizes in the 2 groups (*n*_1_:*n*_2_ = 1:1), our study will require 27 participants in each group. We adjusted the sample size of each group to 30. Considering a dropout rate of maximum 20%, the final sample size was estimated to be 76 participants.

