## Abstract

**Introduction::**

Stable angina pectoris has a high prevalence and causes serious harm. Revascularization therapy can relieve angina pectoris to some extent, but it is not widely accepted in China due to the cost and secondary events. The Chinese proprietary medicine Danlou tablet has been widely used to treat angina pectoris, but previous trials had inadequate methodologies. In this study, we aim to conduct a randomized controlled trial to evaluate its efficacy and safety on stable angina.

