### Statistical analysis

2.16

Statistical analyses consist of 3 parts—baseline comparability analysis, efficacy analysis, and security analysis. An independent statistician will be in charge of the analyses, and Statistical Analysis System (version 9.2) will be used. All tests are 2-sided, and *P* < .05 is considered to indicate statistical significance. According to the intention-to-treat principle,^[32]^ there will be 3 analysis sets: the full analysis set, the per-protocol analysis set, and the safety analysis set. Participants who insist in taking medication for 2 weeks will be involved in the full analysis set group; if a critical variable is missing in any given case, the statistician will consider the last observation result as the final data. Patients who conform to the treatment plan will be included in the per-protocol analysis set group. The Mantel–Haenszel Chi-squared test and analysis of covariance will be conducted in the case of important baseline non-comparability. Normally distributed quantitative data will be presented as mean ± standard deviation and analyzed by Student *t* test. Non-normally distributed quantitative data will be presented as median and interquartile range and analyzed by the Kruskal–Wallis test. Ordinal data, like ECG efficacy, will be analyzed by the Kruskal–Wallis test. Qualitative data will be presented as percentage and rate and analyzed by the Chi-square test and Fisher exact test. The paired Student *t* test will be used to analyze significant differences between pre- and post-treatment. Moreover, subgroup analysis will be conducted according to gender, age, and complications to explore the internal consistency of the conclusions. For the safety analysis, the statistician will adopt the safety analysis set to evaluate the incidence rate of AEs and the change of laboratory indices. Both AEs and laboratory indices are described in lists and analyzed by the chi-square test or Student *t* test.

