## Discussion

3

This study is a WeChat-based block-randomized, double-blind, placebo-controlled, parallel-group clinical trial with the aim of investigating the efficacy of DLT on stable angina. DLT is a Chinese proprietary medicine for the treatment of “intermingled phlegm and blood stasis syndrome” in CAD. Nitroglycerin is usually applied for the acute phase of angina attacks, while long-acting nitrates and trimetazidine are utilized for the relatively stable period. DLT is taken 3 times per day, just like the latter. DLT has been proven effective in clinical trials, animal experiments, cell experiments, pharmacology studies, a metabolomics study, and a network pharmacology study. However, previous clinical studies of SAP may have limitations with respect to randomization, allocation concealment, blinding, and so on. Moreover, previous studies took therapeutic effective rates calculated from ECG efficacy, angina pectoris scores, and TCM syndrome scores as the primary outcomes. Different evaluation standards and study designs lead to greater systematic error. Therefore, we will choose angina frequency as the primary outcome for this study, as it quantitatively, objectively, and specifically reflects the treatment efficacy. Moreover, we will evaluate the degree of coronary artery stenosis by dual-source CT angiography and exclude patients who are diagnosed with myocardial infarction or have a stent implantation, in order to reduce selection bias and confounding factors and to ensure compliance with the patients’ inclusion criteria.

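### Section 2.11 calls margin 0 with the full 0.65 difference the most conservative choice; neither input is, and two-sided power at the planned 30 evaluable per group is about 87%, not 90%

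*Protocol article*

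**What the plan says.** Section 2.11 (Sample size estimation) sizes the trial from one previous study. Weekly angina frequency in its treatment group "was 1.90 ± 0.45 per week, and that in the reference group was 2.55 ± 1.03 per week". The section then explains the remaining inputs: "We wanted to make the most conservative estimate, so we considered the superiority margin as 0 and the true difference as 0.65". It adds a power of 90%, "equal sample sizes in the 2 groups" and the sidedness: "Based on a 2-sided test size of a level of 5" per cent. The result is 27 per group, raised to 30, then 76 in total for a dropout of at most 20%. Section 2.16 (Statistical analysis) uses the same sidedness: "All tests are 2-sided".

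The article also comments on the evidence from which such inputs come. The Abstract says that Danlou tablet is widely used "but previous trials had inadequate methodologies", and the Discussion says that "previous clinical studies of SAP may have limitations with respect to randomization, allocation concealment, blinding, and so on".

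**The concern.** A reader told that the sizing was as cautious as possible will take 90% as a safe figure. But a superiority margin of 0 is the least demanding null in this family, and an observed difference carried over whole leaves no allowance for a smaller true effect. The article's own criticism of earlier trials is a reason for caution about 0.65, and the calculation makes no such allowance. If the power at the planned evaluable size is also below 90% on the stated test, the claim is wrong in both its description and its figure. What is at stake is how a non-significant result is read: as evidence from a trial with power to spare, or from one with moderate power that depends on the full earlier effect.

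**Working it through.** **Inputs (all from section 2.11).** SDs 0.45 and 1.03; means 1.90 and 2.55, so the difference is 2.55 − 1.90 = 0.65; margin 0; 1:1 allocation; two-sided 5%; 90% power; 27, then 30 per group; dropout 20%.

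**Method.** Unequal-variance t test. For n per group, SE = √[(0.45² + 1.03²)/n] = √(1.2634/n). The noncentrality is (true difference − margin)/SE, and power is the noncentral-t tail beyond the critical value, with Satterthwaite degrees of freedom.

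**1. The plan's own figures.**
- n = 27: SE = √(1.2634/27) = 0.2163; noncentrality 0.65/0.2163 = 3.00; df 35.6.
- Two-sided 5%, critical value 2.03: power 83.2%.
- One-sided 5%, critical value 1.69: power 90.4%. The smallest n reaching 90% is exactly 27.
- The smallest n reaching 90% at two-sided 5% is 33 (90.1%). The normal approximation gives 32.
- Dropout: 30/(1 − 0.20) = 37.5, so 38 per group and 76 in total. This step reproduces.

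The stated 27 therefore matches a one-sided 5% test, while sections 2.11 and 2.16 both say two-sided.

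**2. Two-sided power at a true difference of 0.65.**
- n = 30: SE = √(1.2634/30) = 0.2052; noncentrality 3.17; power 87.1%.
- n = 38: SE = √(1.2634/38) = 0.1823; noncentrality 3.56; power 93.8%.

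The equal-variance Student t gives 87.6% and 94.0%, so the choice of t test hardly matters.

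**3. Is margin 0 conservative?** n per group for 90% power at a true difference of 0.65:

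| Margin | Two-sided 5% | One-sided 5% |
|---|---|---|
| 0 | 33 | 27 |
| 0.05 | 39 | 32 |
| 0.10 | 46 | 37 |
| 0.20 | 67 | 55 |

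Margin 0 gives the minimum in both columns. A positive margin shrinks the numerator of the noncentrality, so it can only raise n.

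**4. Is 0.65 conservative?** It equals the observed difference, with a discount of zero. Two-sided power for smaller true differences follows. The size of any reduction is an assumption; the documents give none.

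| True difference | 30 per group | 38 per group |
|---|---|---|
| 0.65 | 87% | 94% |
| 0.60 | 81% | 90% |
| 0.55 | 74% | 84% |
| 0.50 | 66% | 77% |

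**5. Separating the two causes.** On the one-sided basis that reproduces 27, 30 per group would give 92.9% at 0.65, 89.0% at 0.60, 83.9% at 0.55 and 77.3% at 0.50. At 0.55, the gap between 83.9% and the two-sided 74.4% is due to sidedness. The fall from 92.9% to 83.9% is due to the smaller effect.

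**The case against.** The strongest reply has four parts.

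First, margin 0 is the ordinary null for superiority over placebo. That stands: the margin should not change, and the larger n at positive margins measures no shortfall in this trial. It shows only that the description is the wrong way round.

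Second, any trial loses power when the true effect is smaller, and the reduction here is assumed. That also stands, so the sensitivity figures are an illustration and not a forecast. The 87% at 30 per group needs no such assumption; it uses the plan's own difference.

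Third, 30 per group is the result of the maximum dropout. Section 2.13 aims to keep dropout below 20%, and sections 2.5 and 2.16 carry last observations forward. With 34 per group, two-sided power at 0.65 is 91.0%, and with 38 it is 93.8%. This too stands, and it means that 90% must not be called a best case. But 30 is the number that section 2.11 itself plans to have after dropout, and at that number 90% is not reached.

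Fourth, a reader might infer from the phrase "that in the reference group was 2.55 ± 1.03 per week" that the earlier comparator was not placebo, or was unmasked, so that 0.65 must overstate the effect against a masked placebo. The documents do not support this. Section 2.11 does not describe that group, the cited study is not at hand, and the remarks in the Abstract and Discussion concern earlier studies in general. An article that cites a study without describing its control arm is condensing, and that is no fault.

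**Conclusion.** The concern holds in limited form. The conservative label is false for both inputs: margin 0 is the least demanding non-negative margin, and 0.65 is the undiscounted observed difference. The stated 90% is not delivered on the stated two-sided 5% test: power is 83% at 27 per group and 87% at the planned 30 evaluable. It passes 90% at 33 per group and is 94% if all 38 are analysed.

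These figures rest on the plan's SDs and a t test on weekly frequency. The shortfall of about 3 points at 30 per group comes from 27 matching a one-sided test, not from any lost effect. How much lower the power might be depends on a reduction in effect that the documents do not quantify. Nothing here shows that the total of 76 is untenable, that the margin is wrong, or that the earlier comparison was unmasked or not against placebo.

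**What to change.** In section 2.11:

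- Delete the claim that the inputs are the most conservative, and keep margin 0 as the usual superiority null.
- State that 0.65 is the full observed difference from the cited study, without discount.
- Replace the 90% with the two-sided 5% power at the planned size: about 87% at 30 evaluable per group and 94% if all 38 are analysed. Correct the 27, which is the one-sided figure; the two-sided requirement is 33 (32 by normal approximation).
- Add one line or a small table of power at 0.60, 0.55 and 0.50, labelled as an assumption: 81%, 74% and 66% at 30 per group; 90%, 84% and 77% at 38.

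Keep 76 participants. The cost is a few sentences and a less favourable power figure at the planned evaluable size. No patients, visits or analyses are added.

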#### Primary and secondary outcomes

2.8.1

All participants will be required to record the frequency, severity, and duration of angina in the “angina treatment diary.” The “angina pectoris diary” will be presented in the form of an electronic questionnaire, which will be sent to the patients every night via WeChat. The primary outcome is the change in the frequency of angina attacks from baseline to week 4. Secondary outcomes include the severity and duration of angina attacks, TCM efficacy, the withdrawal rate of emergency medications, blood lipid efficacy, and ECG efficacy. The severity of angina will be reported on the basis of the Visual Analogue Scale and the Canadian Cardiovascular Society score (1–2 points, only chest distress, no chest pain; 3–4 points, presence of angina during strenuous ordinary activity; 5–6 points, presence of angina during ordinary activities after meals, in the cold, in the wind, under emotional stress, or during the first few hours after waking up; 7–8 points, having difficulties walking 1 or 2 blocks or climbing one flight of stairs, at normal pace and under normal conditions; 9 to 10 points, no exertion needed to trigger angina). Angina duration refers to the time between the initial onset of symptoms to the time of remission. TCM efficacy is reported on the basis of the Curative Effect of Traditional Chinese Medicine on Coronary Heart Disease Stable Angina issued in 2018.^[30]^ The withdrawal rate of emergency drugs is calculated as follows: withdrawal rate = (number of tablets before treatment − number of tablets after treatment)/(number of tablets before treatment) × 100%. Emergency drugs mainly include nitroglycerin and the SuxiaoJiuxin Pill (another common emergency medicine in China). Blood lipids refer to total cholesterol, triglyceride, low-density lipoprotein–cholesterol, and high-density lipoprotein–cholesterol levels. The ECG efficacy standards are based on the Evaluation Criteria for Efficacy of Coronary Heart Disease Angina Pectoris and ECG (see Table 2). Among these indicators, the angina-related outcomes are derived from the electronic “angina treatment diary,” and other indicators are derived from the CRF. The data collection schedule is shown in Table 3.

**Table 2 T2:** ECG efficacy criteria.

Criteria	ECG changes
Marked effect	The ECG returns to “substantially normal” or reaches “normal ECG.”

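### The stated 27 per group does not follow from the stated two-sided 5% test at 90% power; the printed inputs require 33 per group

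*Protocol article*

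**What the plan says.** Section 2.11 prints a complete set of inputs. From a previous study, the frequency "in the treatment group was 1.90 ± 0.45 per week" and "that in the reference group was 2.55 ± 1.03 per week". The test is two-sided: "Based on a 2-sided test size of a level of 5" per cent, with 90% power and equal groups. On the margin it says: "We wanted to make the most conservative estimate, so we considered the superiority margin as 0 and the true difference as 0.65". The result is that "our study will require 27 participants in each group". This is then raised to 30 per group and, with at most 20% dropout, to 76 in total.

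Section 2.16 (Statistical analysis) agrees on the direction of testing: "All tests are 2-sided", with significance at P < .05 and Student's t test for normally distributed quantitative data.

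On the endpoint, the Abstract (Methods and analysis) gives angina frequency per week as the primary outcome. Section 2.8.1 says: "The primary outcome is the change in the frequency of angina attacks from baseline to week 4".

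**The concern.** Every quantity needed to recompute the sample size is printed, and the printed answer does not come out of it. Both sections that mention the direction of the test say two-sided, so the analysis will be run at a level for which 27 per group does not give 90% power. Rounding up to 30 narrows the gap without closing it.

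What is at stake is how the result is read. If the trial finds no difference, a reader will take the chance of missing a true difference of 0.65 attacks per week as 10%. With the full allowed dropout it is 12-13%.

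Two statements around the calculation also need attention. The remark that a zero margin is the cautious choice is backwards. And the SDs describe weekly frequency, which fits the Abstract's primary outcome but not obviously the change from baseline in Section 2.8.1.

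**Working it through.** **Inputs (Section 2.11).** Means 1.90 and 2.55, so the difference is 0.65; SDs 0.45 and 1.03; margin 0; two-sided alpha 0.05; power 90%; 1:1 allocation.

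**Variance term.** 0.45² + 1.03² = 0.2025 + 1.0609 = 1.2634. The root-mean-square SD is √(1.2634/2) = 0.795.

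**Reproducing the plan's 27.** The normal approximation is n per group = (z_α + z_β)² × 1.2634 / 0.65², with 0.65² = 0.4225.

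- Two-sided 5%: 10.507 × 1.2634 / 0.4225 = 31.4, so 32.
- One-sided 5%: 8.564 × 1.2634 / 0.4225 = 25.6, so 26.

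The noncentral t distribution matches the planned t test:

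| Test | n per group | Power, pooled t | Power, Welch |
|---|---|---|---|
| One-sided 5% | 26 | 89.7% | 89.3% |
| One-sided 5% | 27 | 90.7% | 90.4% |
| Two-sided 5% | 27 | 83.9% | 83.2% |
| Two-sided 5% | 30 | 87.6% | 87.1% |
| Two-sided 5% | 32 | 89.6% | 89.2% |
| Two-sided 5% | 33 | 90.5% | 90.1% |
| Two-sided 5% | 38 | 94.0% | 93.8% |

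The first n to reach 90% is 27 one-sided and 33 two-sided, with either t test. A simulation of 200,000 trials per n gives the same two-sided power: 83.8% and 83.2% at 27, 87.6% and 87.1% at 30, 90.5% and 90.2% at 33 (pooled and Welch). By normal approximation, two-sided power is 85.2% at 27 and 88.6% at 30, still below 90%.

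**Other routes to 27.** The arithmetic mean of the two SDs, 0.74, in the two-sided normal formula gives 27.2, which rounds up to 28, and it is not a valid way to combine SDs. The reference SD of 1.03 alone gives 53.

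**Dropout step.** 30/0.8 = 37.5, so 38 per group and 76 in total. This part reproduces.

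**Loss that the 76 can absorb.** 90% power needs 33 of 38 per group, so 5 of 38 may be lost: 5/38 = 13%. At 20% loss, 38 × 0.8 = 30.4, about 30 per group.

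**Margin.** With a true difference of 0.65, a margin m puts (0.65 − m)² in the denominator. Two-sided t-based sizes are 33 for m = 0, 45 for m = 0.1 and 67 for m = 0.2 (the last two margins are illustrations). A zero margin gives the smallest n.

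**Change scores (illustration only).** The document gives no baseline SD and no baseline to week-4 correlation. Assume 30 per group and an unadjusted pooled t test on change. With a common SD of 0.795 at both visits, power is 75%, 88% and 98% for correlations of 0.3, 0.5 and 0.7. If the printed SDs are instead kept as week-4 SDs with correlation 0.5, power is 94%, 85% and 73% for a baseline SD of 0.45, 0.795 and 1.03. It can move either way.

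**The case against.** The strongest defence concerns consequences, since no reading of the inputs rescues 27 under a two-sided test.

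- **The shortfall is small where it counts.** At 30 evaluable per group it is 1.4 points (normal approximation) to 2.9 points (Welch). With all 76 analysed, power is 94%. Section 2.11 treats 20% as a maximum and Section 2.13 aims to stay below it. This stands, and it is why the point is a correction of text and not a challenge to the design.
- **Dropouts are not all lost.** Section 2.16 admits to the full analysis set those who took medication for two weeks and carries the last observation forward; Section 2.5 also uses dropouts' last data. Later dropouts would thus still count. This softens the practical effect, but Section 2.11 itself inflates as though every dropout were lost, and it does nothing for the 27.
- **The cause is inferred.** No software output is shown. The match with the one-sided calculation is exact at 27, but what can be demonstrated is only that 27 fails to reproduce two-sided.

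Two stronger readings are tempting. A reader might infer that the trial is underpowered and needs more patients; 33 evaluable per group is within reach of 38 randomised, so this does not follow. A reader might also infer that the SDs belong to the wrong endpoint and that power is lower still for change from baseline. The documents do not support that: the Abstract's primary outcome is weekly frequency, which fits the SDs, and the direction of any effect on power depends on a baseline SD and correlation that are not given.

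**Conclusion.** The point holds. The stated requirement of 27 is wrong as written: six per group below the t-based requirement of 33, or five below the normal-approximation figure of 32. Its true two-sided power is 83-84%, which is 6-7 points short of the 90% claimed. The figures assume the printed means and SDs, a difference of 0.65, and a two-sample t test of weekly frequency.

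The practical effect is modest. It appears only when loss from the primary analysis exceeds about 13%, and at the full 20% it costs 2-3 points by t test. The statement about the margin is wrong but changes no number. The endpoint issue is an inconsistency between the Abstract and Section 2.8.1, not a demonstrated loss of power. Should-fix.

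**What to change.** Keep 76 participants and rewrite the paragraph in Section 2.11, for example: 33 evaluable participants per group give 90% power for a difference of 0.65 attacks per week at a two-sided 5% level (SDs 0.45 and 1.03, t test); with 76 randomised and 20% lost, about 30 per group remain and power is about 87%; 90% is kept if no more than about 13% are lost from the primary analysis.

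Delete the claim that a zero margin is the conservative choice. State that the SDs and the power refer to weekly angina frequency, and make the Abstract and Section 2.8.1 agree on whether the primary outcome is weekly frequency or its change from baseline. If change from baseline is retained and analysed unadjusted, give the assumed baseline SD and correlation and the power that follows.

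The cost is one reworded paragraph, one aligned definition and a slightly less favourable power statement. No extra patients are needed. If the sponsor prefers to guarantee 90% at the full 20% dropout, 33/0.8 = 41.25, so 42 per group and 84 in total, eight more than planned.
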